### Study treatment

Participants will be randomised to commence treatment on either PGB or GBP. As a result of the cross-over methodology, participants will have the opportunity to experience both PGB and GBP, and we predict little or no carry-over effects (medium- or long-term) after the washout period. We believe the incorporation of a stand-alone placebo arm is unethical in trials where participants with moderate to severe pain are recruited.

The starting dose of PGB is 150 mg once daily for the first week. This will be titrated to the participant’s optimal dose up to a maximum of 300 mg twice daily, depending on their progress and tolerance at each dose level. The starting dose for GBP is 400 mg once daily for the first week. This will be titrated to the participant’s optimal dose up to a maximum of 800 mg thrice daily, depending on their progress and tolerance at each dose level. These doses are based on national recommendations from the Australian Medicines Handbook [11]. In the standard study dosing regimen (Table 1), we expect a 4-week titration period, after which the maximum tolerated dose for each participant will be maintained for 4 weeks before the first study medication is ceased in preparing for washout. The washout period between treatment phases will last 1 week, which is sufficient for these medications because they possess a short half-life (5–7 h). The dosage of either PGB or GBP can be amended at any stage in PAGPROS on the basis of efficacy and/or SEs by communication between the study specialist and the study pharmacist. The maximum treatment period is 8 weeks [13].

**Table 1 Tab1:** PAGPROS medication titration schedule

	Medication	Total daily dose
Week	Pregabalin	
1	1 × 150-mg capsule in the morning	150 mg/day
2	1 × 150-mg capsule three times daily (middle dose is placebo)	300 mg /day
3–8	2 × 150-mg capsules three times per day (middle dose is placebo)	600 mg/day
Week	Gabapentin	
1	1 × 400-mg capsule in the morning	400 mg/day
2	1 × 400-mg capsule three times per day	1200 mg/day
3–8	2 × 400-mg capsules three times per day	2400 mg/day

*PAGPROS* Pregabalin and Gabapentin Prospective Clinical Trial for the Treatment of Sciatica: A Randomised, Double-Blind, Cross-over Study

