Participating in PAGPROS is completely voluntary, and participants can stop taking part at any time without explanation or prejudice. Ceasing to participate in PAGPROS may be considered, for example, wherever participants wish to explore the possibility of other treatments, including other medications or interventions (*see above*). In some cases, participants may find that the starting dose of either PGB or GBP, whilst efficacious, produces unwanted SEs [10]. In such cases, a lower dose may be required, at least for a period of time. Because this cannot be accommodated within the current PAGPROS protocol, such patients will be removed from the study, and their data will be analysed as per intention-to-treat (ITT) principles; however, they may still form part of a prospective cohort for parallel study.

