### Adverse experiences and monitoring

Potential risks of both PGB and GBP have been well studied owing to their use for neuropathic conditions. These risks have been minimised by our exclusion criteria. Any SEs will be monitored weekly during follow-up phone calls and examinations. Close monitoring of other neurological pain medications will be done with patient diaries. SEs were quantified in a latest meta-analysis and given the rare SEs of both medications and their likely effectiveness, and the potential benefits outweigh the risks in this study [1].

During the recruitment period, a monitoring visit may be applicable. The responsible monitor will be a specialist neurosurgeon who is not involved in the conduct of the trial and is chair of the hospital patient safety committee. The purposes of monitoring are as follows:To ensure that the study is conducted according to the protocol and applicable guidelines and regulationsTo verify source data against data on the CRF and in the databaseTo check the security of stored dataTo confirm that the consent process, approved by the Townsville Hospital Human Research Ethics Committee, has been followed and to view a random sample of original signed consent formsTo review all serious adverse events (SAEs)

Interim data monitoring will take place in-house for review of safety and SEs. The trial may be stopped if more harm to patients is shown. The Pocock boundary will be used as the stopping rule, whereby after each set of 2n patient responses to a total of ‘K’ looks at the data. "2n" patient responses means there will be at least 2 interim analyses whereby the stopping rule can be enforced. This will be a group sequential approach whereby the critical boundary (*p* < 0.018) will be set at each look.

An adverse event is the appearance or worsening of any undesirable sign, symptom or medical condition occurring after starting the study, even if the event is not considered to be related to the investigational drug. Any SAE (defined as an event that is life-threatening or results in death, hospitalisation or significant disability) will be reported immediately to the relevant authorities (study monitor, ethics committee, data and safety monitoring board). If a potential relationship is suspected between the study drug and an SAE, then un-blinding to treatment allocation is indicated, and the participant will be withdrawn from PAGPROS.

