Finally, the double-blind cross-over design of PAGPROS may provide guidance regarding the implications of any potential need to substitute one drug for the other. For example, PAGPROS may determine whether SEs experienced with one drug are also observed with the other (i.e., in the same patient, in close temporal succession after cross-over). This may prove especially important should PAGPROS demonstrate a between-groups null effect regarding efficacy. However, PAGPROS may show significant efficacy to one drug but no efficacy to the other. Despite a lack of an evidence base, many formulary regulatory authorities worldwide typically favour one drug for subsidy over the other [4]. This hinders interchange wherever the favoured drug is either ineffective or not tolerated [4]. The nature of PAGPROS’s design will directly assess the utility of cross-over between PGB and GBP and will therefore enable formulary regulatory authorities to make more informed therapeutic decisions than currently.

Recruitment commenced in early 2016, with data collection to be completed by mid 2018. The allocation concealment and double-blind design minimise bias, and data collection processes ensure data quality and integrity. The trial team has extensive experience in the design, conduct and reporting of clinical trials. Results of the study will be disseminated via publications and presentations.

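### Recurrence of side effects from one drug to the other can be estimated only in patients who stay through cross-over, which is narrower than the Discussion's claim about substitution where a drug is not tolerated

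*Protocol article*

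**What the plan says.** The Discussion of the protocol article gives the cross-over a second use beyond efficacy: "PAGPROS may determine whether SEs experienced with one drug are also observed with the other". It specifies that this is seen "in the same patient, in close temporal succession after cross-over". The same paragraph names the problem to be informed, namely formularies that subsidise only one of the drugs: "This hinders interchange wherever the favoured drug is either ineffective or not tolerated". It ends more firmly, stating that the design will assess directly how useful crossing between the drugs is, so that regulators can decide on better information.

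Two rules in the Methods bear on who reaches the second drug.

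- Study treatment foresees that "participants may find that the starting dose of either PGB or GBP, whilst efficacious, produces unwanted SEs" and that a lower dose may then be needed. It continues: "Because this cannot be accommodated within the current PAGPROS protocol, such patients will be removed from the study". Their data are analysed by intention to treat, and "they may still form part of a prospective cohort for parallel study".
- Adverse experiences and monitoring says that, if a serious adverse event is suspected to be drug-related, "un-blinding to treatment allocation is indicated, and the participant will be withdrawn from PAGPROS".

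Study treatment also says: "The dosage of either PGB or GBP can be amended at any stage in PAGPROS on the basis of efficacy and/or SEs".

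The frequency and severity of side effects is the key secondary outcome, collected at weeks 4, 8, 10, 14 and 18 (Secondary objective and outcome). The section Potential weaknesses of PAGPROS covers treatment duration, dosages and background therapy. It does not mention loss of patients before the second drug.

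**The concern.** To see whether a side effect recurs, the same patient must take both drugs. A patient removed or withdrawn during the first period has no observation on the second drug, and the article describes no early move to the second drug and no follow-up on it after removal. These patients are the clearest cases of a first drug that was not tolerated, so they are the ones for whom a formulary body most needs to know whether the other drug is an option.

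Two things are at stake. First, the substitution conclusion would rest on patients who managed at least the starting dose without a suspected drug-related serious event. Second, side-effect rates in period 2 describe a group already filtered by the first drug. If the two drugs differ in tolerability, the filter differs by sequence, so period 2 no longer compares the groups as randomised. Period 1 still does.

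**Working it through.** **Who reaches the second drug, from the text**

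| Experience on drug 1 | Rule | Observed on drug 2? |
|---|---|---|
| Mild side effects | no removal rule | yes, weeks 14 and 18 |
| Side effects above the starting dose | titration to tolerance, dose amendment (Study treatment) | yes, if they stay |
| Cannot take the starting dose | removal (Study treatment) | no provision |
| Suspected drug-related serious event | unblinding and withdrawal (Adverse experiences and monitoring) | no provision |

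Intention-to-treat analysis keeps the first-period data of removed patients, but it cannot create side-effect data for a drug never taken. Nor can last observation carried forward (Data integrity and analysis). If that rule were applied to side effects across periods, it would copy drug-1 events into drug 2. The article does not say that it would be used in this way.

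**The plan's own figure**

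Sample size gives 30 evaluable patients, 20% drop-out, and a total of 38, or 19 per sequence. Check: 30 / (1 − 0.20) = 37.5, rounded up to 38. This reproduces.

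**How many could be lost before drug 2**

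- Planned drop-out, all causes and both periods: 0.20 × 38 = 7.6. Split evenly between sequences, 0.20 × 19 = 3.8. At the planned rate this is a ceiling per sequence, because it counts every loss as a first-period loss for side effects.
- Illustration from the Discussion, where 31% stopped gabapentin within a week in a prior study: 0.31 × 19 = 5.9 of the gabapentin-first patients, leaving about 13. The article gives no reasons for stopping, and the figure exceeds the trial's own drop-out assumption. It gives no corresponding figure for pregabalin.

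**How many patients with drug-1 side effects would still cross over**

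The Dosages paragraph quotes side effects in 53% of a gabapentin cohort. Assume that this holds for either first drug: 0.53 × 38 = 20.1 patients. If all 7.6 planned drop-outs came from them, 7.6 / 20.1 = 38% would be unseen on drug 2 and 20.1 − 7.6 = 12.5 would remain. Recurrence could therefore be estimated for many patients with side effects, but not for those removed.

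**Direction of the selection**

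Let p be the share intolerant of each drug (assumed equal), and c the chance of being intolerant of drug 2 given intolerance of drug 1. If everyone intolerant of drug 1 leaves, intolerance of drug 2 among those who cross over is (p − p·c) / (1 − p).

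| p (assumed) | c = p (independent) | c = 0.5 | c = 0.8 |
|---|---|---|---|
| 0.20 | 0.16 / 0.80 = 20% | 0.10 / 0.80 = 12.5% | 0.04 / 0.80 = 5% |
| 0.31 | 0.2139 / 0.69 = 31% | 0.155 / 0.69 = 22% | 0.062 / 0.69 = 9% |

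The more intolerance is shared between the drugs, the lower the period-2 rate looks. For intolerance of this degree, c itself is not observed at all.

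**The case against.** The strongest reply is that removal is narrow. It applies to intolerance of the starting dose, which Table 1 shows to be the smallest step in the schedule. Patients with side effects at higher doses are titrated to tolerance, stay, cross over and are recorded on both drugs. This stands. A reader might infer that drug-2 side effects are seen only in patients who tolerated drug 1 for the full 8 weeks; the documents do not support that.

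A reader might also see a flat contradiction between the freedom to amend the dose at any stage and the statement that a lower dose cannot be accommodated. The two can be read together as amendment above a starting-dose floor. This also stands: the wording is unclear, but a contradiction is not shown.

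Third, the sentence on recurrence is hedged and limited to what is seen after cross-over. This stands in part. The paragraph's closing statement about assessing the utility of cross-over carries no such hedge, and the setting that it addresses includes drugs that are not tolerated.

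Fourth, the article specifies no pooled two-period side-effect analysis, and tabulation detail belongs in an analysis plan that is not shown. That is right, and no missing analysis is alleged. The point rests on a stated claim set against stated removal rules. Some loss before period 2 is common in cross-over trials, but here it falls on the patients whom the substitution claim is about, and the listed weaknesses omit it.

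**Conclusion.** The point holds in limited form. The trial can estimate recurrence of side effects among patients who remain through cross-over, including those with milder side effects or side effects at higher doses. It cannot do so for patients removed on drug 1 because they could not take the starting dose or had a suspected drug-related serious event. Period-2 side-effect rates come from a selected group.

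The size of the selection is not known. At the planned drop-out, evenly split, the ceiling is about 4 of 19 per sequence. About 6 of 19 is an illustration only, since it assumes that the prior study's stopping rate carries over and was due to side effects. The direction, towards understating intolerance of the second drug, depends on intolerance being shared between the drugs; under independence there is no such shift.

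A reader might infer that the efficacy comparison or the whole side-effect comparison is invalid. Neither follows: nothing here bears on the co-primary outcomes, and first-period side effects remain a randomised comparison.

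**What to change.** 1. In the Discussion, limit the statements on recurrence and on the utility of cross-over to patients who remain in the trial through cross-over, and add the selection to Potential weaknesses of PAGPROS.
2. Report side effects and stopping in period 1 by randomised group, with denominators by sequence for both periods, beside any two-period comparison of the key secondary outcome.
3. Reconcile the two statements in Study treatment on when a dose reduction for side effects can be accommodated, and state whether a patient who stops drug 1 may enter period 2. That decision belongs to the investigators; the statistical need is only that the rule be clear, because it determines who is observed on drug 2.

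The cost is wording and one tabulation from data already collected. The downsides are a narrower interchange claim and a period-1 comparison that is less precise, because it compares 19 patients with 19 and does not use each patient as his or her own control.

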### Potential weaknesses of PAGPROS

#### Treatment duration

PAGPROS permits a 4-week titration period, after which the maximum tolerated dose for each participant will then be maintained for 4 weeks. The duration of individual drug study is therefore 8 weeks. In some rare cases, this might be considered insufficient to test efficacy at the optimum dose [10]. Furthermore, because anecdotally some patients develop tolerance to SEs incurred with either PGB or GBP, the study period may also be too short to detect SE tolerance.

#### Dosages

Given the restricted doses and study time available in PAGPROS, it is not possible to introduce either drug in ‘low and slow’ fashion [4]. Because the latter potentially off-sets the development of SEs [4], PAGPROS may therefore potentially over-estimate SEs with either drug. However, at least with GBP, there exists some control in that a prospective cohort study found SEs in 53% of patients with CS [10].

#### Maintenance of background therapies including prior analgesia

This may affect both efficacy and SE development, potentially increasing both. However, note that this practice is entirely consistent with NICE-UK guidelines [6, 10], and, indeed, standard clinical practice. NICE-UK guidelines state that, when super-adding second-line analgesic agents (such as GBP and PGB), ‘overlap with first-line agents is encouraged to avoid decreased pain-control’ [6]. To our knowledge, only one prospective cohort study has reflected this practice using GBP in CS [10].

### Trial status

Screening for patients for this trial began on 7 March 2016. The first patient was included on 4 April 2016. To date, 18 participants have successfully completed the trial, and inclusion is expected to run until 31 June 2018.

## Abbreviations

ATG: Australian Therapeutic Guidelines
CONSORT: Consolidated Standards of Reporting Trials
CRF: Case report form
CS: Chronic sciatica
GBP: Gabapentin
HLOC: Health Locus of Control Scale
ITT: Intention to treat
NICE-UK: National Institute for Health and Care Excellence – United Kingdom
NP: Neuropathic pain
NSAID: Non-steroidal anti-inflammatory drug
ODI: Oswestry Disability Index
PAGPROS: Pregabalin and Gabapentin Prospective Clinical Trial for the Treatment of Sciatica: A Randomised, Double-Blind, Cross-over Study
PBS: Australian Pharmaceutical Benefits Scheme
PGB: Pregabalin
SAE: Serious adverse event
SE: Side effect
SPIRIT: Standard Protocol Items: Recommendations for Interventional Trials
TCA: Tricyclic antidepressant
VAS: Visual analogue scale
